## Abstract

**Abstract:**

**Introduction:**

Developments in blood biomarkers (BBMs) in dementia call for studies that evaluate their diagnostic, prognostic and societal implications in real-world populations. Such evidence is essential to support the safe and effective integration of BBMs into clinical practice.

**Methods and analysis:**

The REAl world Dementia OUTcomes study (READ-OUT) is a UK-based, multi-site study that assesses the prognostic and diagnostic utility of BBMs in people attending memory assessment services (‘secondary care’). READ-OUT phase 1 is a 3-year observational study of 3165 people representative of the UK population, with up-sampling of under-represented groups and proactive recruitment to include individuals missing from secondary care memory services. Participants are over the age of 45, able to provide a blood sample and willing to consent to linkage with electronic health records. The baseline study visit includes venepuncture and questionnaire assessment of quality of life and health resource usage. A subsample of the full cohort will have further venepuncture and questionnaires at a 52-week follow-up. READ-OUT substudies will evaluate BBMs’ test–retest reliability, the impact of processing delays and the feasibility of self-collected blood-spot samples. The clinical utility of BBMs will be assessed against diagnosis, outcomes from electronic health records, corollary data and health economic data. Results of the observational study discussed in this protocol will inform the design of a randomised controlled trial to test the cost-effectiveness, acceptability and clinical utility of disclosed BBM results.

**Ethics and dissemination:**

The study has received Research Ethics Committee approval (REC reference 24/WA/0330) and approval through the Health Research Authority/Health and Care Research Wales (IRAS project 342412). Anonymised study data will be stored on the Dementia Platform UK (DPUK) Data Portal (https://portal.dementiasplatform.uk) and made available through a managed access process, subject to the DPUK Data Access Agreement.

STRENGTHS AND LIMITATIONS OF THIS STUDYREAl world Dementia OUTcomes (READ-OUT) is a multi-centre real-world cohort of the diagnostic and prognostic utility of blood-based biomarkers in N=3165 people with cognitive and behavioural symptoms.This study evaluates blood biomarkers for dementia in a cohort that reflects the diversity of the UK population.Thresholds for optimal biomarker performance will be informed by patient/carer input.Results of READ-OUT’s observational study will determine the second study phase, a randomised controlled trial of biomarker disclosure.Diagnostic confirmation will draw on expert review of notes, longitudinal follow-up, with gold standard genetics, positron emission tomography and neuropathology in a subset of patients.

## Introduction

 The number of people living with dementia and neurodegenerative disease is rising in the UK and globally,^1 2^ with costs for the individual, their families and carers, and wider society.^3^,^5^ There is a pressing need for accurate and early diagnosis of dementias, supporting clinical pathways and anticipated disease-modifying treatments that are specific to the underlying neuropathology. Early and accurate diagnosis allows instigation of effective interventions and support at a point when a person with dementia is able to make decisions about their care,^5^ and reducing the anxiety and carer burden arising from diagnostic uncertainty and delay.^46^,^8^ The management of dementia is evolving, driven by positive phase three trials of disease-modifying therapies for Alzheimer’s disease (AD),^9 10^ which require confirmation of amyloid positivity.

The current diagnosis of dementia in memory clinics typically rests on a combination of clinical assessment, neuropsychological testing and neuroimaging by MRI or CT.^11^ Clinical and cognitive assessments can be inconclusive or incorrect even at expert memory centres,^12^ while standard structural imaging and clinical biomarkers lack molecular specificity even where the clinical diagnosis is correct. A small proportion of patients at UK memory centres have access to pathologically specific biomarker testing through positron emission tomography (PET) imaging or lumbar puncture, but these are resource-intensive and not widely available.^13 14^

Recent developments have highlighted the potential use of blood tests reflecting the underlying pathology of dementia, particularly the beta-amyloid burden in AD.^15^,^22^ In research cohorts, they have been shown to accurately differentiate individuals with AD when compared with clinical diagnoses,^17^ gold standard PET or cerebrospinal fluid (CSF) biomarkers^23 24^ and amyloid neuropathology.^25^ Blood biomarkers (BBMs) have also been shown to have prognostic value both in people with dementia and in at-risk cohorts.^1626^,^28^ Novel CSF biomarker developments may enable identification of non-amyloid pathology in neurodegenerative disease,^29^ but BBMs of these pathologies are not yet validated for clinical practice.

Although BBMs have the potential to improve diagnostic accuracy and prediction of outcomes for people with dementia, they are not yet integrated into standard practice within health services, including the UK National Health Service (NHS). Research study cohorts are younger, less comorbid and less ethnically diverse than patients in real-world memory services^30^ and so further work is needed to establish the utility and efficacy of such tests in well-powered real-world (‘minimally selected’) populations.^31 32^ In addition, knowledge about the impact on biomarker-based diagnosis for people with dementia is incomplete, including our understanding of whether people want to know the results of imperfect tests, what they want to know, and how this information is best conveyed.^33^,^35^

The REAl world Dementia Outcomes (READ-OUT) study assesses the diagnostic and prognostic utility of BBMs for people attending memory clinics, in a participant group representative of the diversity of people with dementia or cognitive symptoms in the UK. The study is divided into two consecutive phases, with phase 1 consisting of a 3-year observational study of 3165 people, followed by a randomised controlled trial of disclosure (phase 2). Recruitment for READ-OUT builds on the Dementia Platform UK (DPUK) Trial Delivery Framework (TDF), a network of NHS hospital services, healthcare commissioners, higher education institutions and NHS primary care networks. This network enables rapid, cost-effective recruitment of accurately characterised individuals to assess BBMs.

BBMs are considered in three *Tiers* determined by the current research evidence or clinical practice: tier 1 tests have either phase 3 clinical evidence, meeting standards set out by the Alzheimer’s Association,^36^ or are in current healthcare use; tier 2 tests have extensive research evidence but without evidence meeting criteria for tier 1; and tier 3 includes other, novel or exploratory biomarkers. READ-OUT will initially test tier 1 and tier 2 biomarkers, and retain serum, plasma and DNA (without cells) for tier 3 BBM work in partnership with academic and industry groups. This protocol focuses on phase 1 of the study, with a further protocol to be published detailing the second study phase. The research questions of the combined study are set out in the following section.

### Summary of research questions

READ-OUT is designed to test hypotheses associated with five central research questions across the observational study arm (READ-OUT phase 1) and randomised controlled trial (READ-OUT phase 2). Research questions 1–3 will be addressed in the observational study arm, while questions 4–5 will require data from the combined READ-OUT phase 1 and phase 2 studies.

What is the utility of BBMs for people in memory assessment services?Which BBMs are needed to test the hypothesis that BBMs are cost-effective and ready for healthcare application?How do BBMs perform in terms of their:Diagnostic utility for the accuracy of detection of AD and non-Alzheimer’s dementias?Prognostic utility?Variance arising from characteristics of individual participants, including sex, age, multimorbidities, ethnicity, level of deprivation?Utility within clinical pathways from the viewpoints of stakeholders?Which BBMs give optimal performance?Which biomarker or set of biomarkers is useful for dementia diagnosis and prognostication?How do BBMs perform when considering complementary validations, against:Clinical assessment, including the use of brain imaging.Long-term electronic health record linkage.Selected case reviews by independent experts, against disease-specific consensus criteria.Comparison with genetics, CSF biomarkers and amyloid-PET imaging.What mode of blood-based biomarker assessment gives optimal performance in real-world populations? READ-OUT considers the challenges to biomarker service delivery, including whether:BBMs are robust to processing delays?Phlebotomy can be substituted by remote blood test kits, such as blood-spot cards, including where these are posted to or from participants?Test–retest reliability is sufficiently high for management decisions for individual patients?What are the effectiveness and cost-effectiveness of BBMs? READ-OUT assesses the intended applications of BBMs in clinical practice in terms of:Biomarker impact on health outcomes.Total lifetime healthcare costs.Quality-adjusted life years.Cost-effectiveness and impact on budgets, including impact on affordability, implementation in clinical practice and variance depending on timing in the clinical pathway.Quantitative and qualitative evaluations of blood-based biomarker testing and disclosure, to understand what information patients want and the communication of risk and effectiveness.How do we ensure a blood-based biomarker pathway that is scalable and sustainable?What is required for a sustainable, scalable national health services model for BBMs?How can BBMs be delivered across the UK?

## Methods and analysis

### Study design

The READ-OUT study protocol consists of two consecutive phases designed to address the research hypotheses. The first phase (figure 1) is a 3-year observational-design study in 3165 people using a broad panel of BBMs, with a 52-week follow-up in 20% of participants. The study started on 1 November 2024. The study baseline visit includes blood sampling, self-reported instruments to assess health and health resource usage, and collation of demographic details and medical history. Substudies will investigate the effect of sample processing delays, test–retest reliability of BBMs and the utility of blood spot cards. In the third year of the study, a panel of experts, including people with lived experience of dementia and their carers, will review the evidence from the observational study to determine BBM choices and generate clinician and patient-facing materials detailing the significance of the BBM results.

**Figure 1 F1:**
[figure not shown]
Schematic of the study design for REAl world Dementia OUTcomes (READ-OUT) phase 1. Participants (N=3165) are recruited from centres in the Dementia Platform UK (DPUK) Trial Delivery Framework. Blood-based biomarkers are considered in three tiers depending on research evidence and current clinical use. Diagnostic and prognostic utility will be assessed with a range of statistical methods, including incorporating linked clinical data. Thresholds will be determined with feedback from the patient and participant involvement and engagement group, and health economic impact using information from Integrated Care Boards (ICBs). Results of the observational arm of READ-OUT will feed into a randomised controlled trial (RCT) of blood-biomarker results disclosure. CSF, cerebrospinal fluid; EHR, electronic health record; MDT, multidisciplinary team; PET, positron emission tomography; PPIE, public and patient involvement and engagement.

Phase 2 of READ-OUT is a randomised controlled trial to test the cost-effectiveness, acceptability and clinical utility of disclosed BBMs to patients and their clinicians. The final protocol for READ-OUT phase 2 will be set out in detail in a further publication.

### Participant recruitment and selection

The observational phase of READ-OUT will recruit 3165 participants. Participants are over the age of 45, able to provide blood samples and willing to consent to linkage to NHS health records (box 1). There are no restrictions on diagnosis or severity. People with cognitive symptoms attending secondary care services for dementia and related conditions (‘memory clinics’) are eligible, regardless of the diagnosis emerging from assessment in those services. Participants must provide informed consent, unless the participant does not have capacity for consent to study participation, in which case advice will be sought from a consultee or their guardian/attorney as set out in the relevant legislation in the devolved nations of the UK.

Box 1Inclusion and exclusion criteria for READ-OUT phase 1Inclusion criteriaAged 45 or above.Referred or referable with cognitive or behavioural symptoms and/or diagnosed with a cognition-related disorder; including those with subjective cognitive impairment and functional disorders.Willing and able to give informed consent for participation in the study.ORAdults who otherwise lack the capacity to consent, but for whom advice regarding participation has been obtained via a consultee using the personal consultee process.Exclusion criteriaLack of venous access.Unwilling to consent to NHS data linkage.NHS, National Health Service; READ-OUT, REAl world Dementia OUTcomes.

90% of participants will be recruited from memory clinics at selected clinical sites across the UK embedded within the DPUK TDF. Participants will be approached by their clinical team, or by affiliated researchers, where they are part of a relevant research registry or cohort. Contact information for interested participants will be forwarded to the site study team. The further 10% of participants will not currently be in secondary care services but would be eligible for referral to secondary care memory services. This group is loosely defined, in order to account for the under-representation of certain communities and individuals from regions of higher socioeconomic deprivation in current UK memory services, who in other contexts would be expected to be in contact with secondary care services for their symptoms. Participants will be identified by primary care providers based at DPUK TDF sites who will search for individuals who have either evidence for subjective or objective cognitive difficulties, or a history of recurrent delirium, and no recorded diagnosis of a cognitive disorder. Primary care providers will contact the participant and will pass on contact details to the local study team with the participant’s permission. Following the study visit, relevant information will be passed on to the participant’s primary care provider with their agreement for consideration of further work-up or referral as needed.

READ-OUT aims for 30% recruitment in traditionally underserved and under-represented groups based on ethnicity, comorbidities and socioeconomic deprivation. To achieve this aim, we use census and community mapping to prioritise recruitment at DPUK TDF and DPUK Partner Akrivia Health sites, and from DPUK’s Feasibility and Acceptability of Scalable Tests of brain health study and ON-FIRE frontotemporal dementia study. We will prioritise sites with high levels of under-represented populations, using the NIHR-INCLUDE guidelines and NIHR-INCLUDE Ethnicity Framework.^37^ This will be supported by a range of outreach techniques, including the use of community connectors, telemedicine, education around brain health, research buses aligned to memory services and the development of language and culturally specific study information.

### Sample size and power

Given that the assessment of clinical utility of BBMs requires accuracy, READ-OUT prioritises receiver operator characteristics. Diagnostic and prognostic performance metrics are accuracy, sensitivity, specificity and positive- and negative-predictive values. A cohort size of N~3000 allows comparison of tests in subgroups with multiple predictors to detect events (dementia diagnosis, dementia aetiology, prognostication) and greater than 10 events per predictor using unbiased logistic regression, machine learning approaches, and out-of-sample testing.^38 39^ Power for individual tests will vary according to the prevalence of each dementia type in the cohort. Indicative frequentist power calculations were performed in R V.4.4.1 using the *powerMediation*^40^ packages. For example, we assume rates of mild cognitive impairment (MCI) of 17% in line with UK memory clinic^41^ with annual conversion rates from MCI to dementia of 10%–15%.^42 43^ A cohort of N=3165 gives 80% power at 5% significance to detect a change in the probability of converting to dementia within a year from 10% to 15% (an OR of 1.5) when the BBM is increased by 1 SD above the mean.

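### The power example equates a rise from 10% to 15% with an odds ratio of 1.5, but that rise is an odds ratio of 1.59; the stated 80% power fits 1.5, so the slip is conservative

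*Protocol article*

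**What the plan says.** All the relevant text is in the Sample size and power section of the protocol article. It sets the share of the cohort with MCI: "we assume rates of mild cognitive impairment (MCI) of 17% in line with UK memory clinic". It takes annual conversion from MCI to dementia to be between 10% and 15%. It then states that "A cohort of N=3165 gives 80% power at 5% significance". The target it names for that power is this: "detect a change in the probability of converting to dementia within a year from 10% to 15% (an OR of 1.5"), per increase of 1 SD in the biomarker.

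The calculation is labelled indicative, is introduced as an example, and is attributed to an R package for power calculations. It is the only place in the article where a sample size is tied to an effect size and a power. The same section also supports a cohort of about 3000 on separate grounds, namely subgroup comparisons and more than 10 events per predictor.

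**The concern.** The sentence offers a pair of probabilities and an odds ratio as the same effect, and they are not. The ratio of the probabilities, 0.15/0.10, is 1.5, so a risk ratio appears to have been labelled as an odds ratio. Logistic regression is one of the article's named methods and works on the odds scale, so the difference affects the power.

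At stake is whether a reader can tell which effect has 80% power. Someone who repeats the calculation from the two printed probabilities will not recover 3165. The sentence also has to be right if it is carried into the full protocol or the analysis plan.

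**Working it through.** **Inputs from the section:** N = 3165; power 80%; significance 5%; MCI share 17%; conversion probability 10% at the biomarker mean and 15% at 1 SD above it; odds ratio per SD 1.5.

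**Assumptions, because the section does not state them:** the test is two-sided; the formula is the simple one for logistic regression on one standardised continuous predictor; the people analysed are those with MCI, 0.17 × 3165 = 538.05, about 538. If all 3165 were analysed, power would exceed 99.9% for either effect, so the MCI reading is the only one of the two compatible with the stated 80%.

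**Step 1. Do the probabilities and the odds ratio agree?** This step needs none of the assumptions.
- Odds at 10%: 0.10/0.90 = 0.1111. Odds at 15%: 0.15/0.85 = 0.1765.
- Odds ratio: 0.1765/0.1111 = 1.588. To one decimal this is 1.6, so rounding does not explain 1.5.
- Conversely, 1.5 × 0.1111 = 0.1667, and 0.1667/1.1667 = 0.1429, that is 14.3%.

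**Step 2. Reproduce the plan's figure with the odds ratio of 1.5.** The formula is n = (z₀.₉₇₅ + z₀.₈₀)² / [p(1−p)(ln OR)²], with p = 0.10.
- (1.960 + 0.842)² = 7.849; p(1−p) = 0.09; ln 1.5 = 0.4055.
- n = 7.849 / (0.09 × 0.1644) = 530.5 people with MCI, rounded up to 531.
- N = 530.5/0.17, about 3,120 (3,124 from 531). This is within 1.5% of 3165.
- Power with 538: Φ(√(538 × 0.09) × 0.4055 − 1.960) = Φ(0.861) = 80.6%.

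**Step 3. Repeat with the effect the probabilities describe.** ln 1.588 = 0.4626.
- n = 7.849 / (0.09 × 0.2140) = 407.5, rounded up to 408; N = 407.5/0.17, about 2,397 (2,400 from 408).
- Power with 538: Φ(√(538 × 0.09) × 0.4626 − 1.960) = Φ(1.259) = 89.6%.

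**Step 4. Check by simulation.** Fitting a logistic regression to 3,000 simulated data sets of 538 people gave 81.3% power at an odds ratio of 1.5 and 90.2% at 1.588.

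**Step 5. Vary the assumptions.**

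| Variant | N, OR 1.5 | N, OR 1.588 |
|---|---|---|
| Two-sided, p = 0.10 | 3,124 | 2,400 |
| One-sided, p = 0.10 | 2,459 | 1,888 |
| Two-sided, p = 0.125 | 2,571 | 1,976 |
| Two-sided, p = 0.15 | 2,206 | 1,694 |
| Whittemore/Hsieh correction, two-sided, p = 0.10 | 3,462 | 2,687 |

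Only the first variant, with an odds ratio of 1.5, comes close to 3165. No variant does so with 1.588. A two-group comparison of 10% against 15% needs 1,372 people with MCI, N about 8,071, but the section describes a change per SD of a continuous marker, not two groups.

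**The case against.** The case for leaving this alone has several fair parts.

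- **The error costs the study nothing.** Under the formula that reproduces the plan's figure, and in simulation, neither effect falls below 80% at 538 people with MCI. The 10% to 15% change has more power than claimed, and the two effects differ by only 0.7 percentage points at 1 SD (15.0% against 14.3%). This stands, and it limits the weight of the point. A reader might infer from a faulty power statement that the study is underpowered; the figures show the opposite for the printed probabilities.
- **The calculation is illustrative.** The section says that power will vary with the prevalence of each dementia type, and it gives priority to accuracy metrics. This also stands. It lowers the stakes but does not make the two effects equal.
- **The cohort size does not rest on this sentence alone.** A reader might take it as the sole justification of N, but the section gives the events-per-predictor argument as well. What can be said is that this is the only numerical power statement.
- **The origin of N is not documented.** It is tempting to say that 3165 was derived from an odds ratio of 1.5. The section says only that this cohort gives 80% power. The sidedness, the formula and the division by 17% are all reconstructed, the nearest match is still about 41 short (3165 − 3124), and the Whittemore/Hsieh variant gives 3,462. The derivation is a well-supported inference and no more.

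None of this touches Step 1, which depends only on the printed figures.

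**Conclusion.** The point holds as an arithmetic inconsistency of minor weight. The article's one numerical power statement presents an odds ratio of 1.59 and an odds ratio of 1.5 as the same effect; this follows from the printed numbers without any assumption.

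Which of the two carries the stated power does rest on assumptions: a two-sided 5% test, the simple logistic formula, 10% conversion at the biomarker mean, and about 538 people with MCI. Under these, the 80% belongs to the odds ratio of 1.5, and the printed change in probability has about 9 points more. The error is conservative. It gives no reason to question the cohort size, the recruitment or the analysis.

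**What to change.** Rewrite the indicative example so that the probabilities, the odds ratio and the power agree. Either version will do:
- 80% power for an odds ratio of 1.5 per SD, corresponding to 10% rising to 14.3%; or
- about 90% power for 10% rising to 15%, corresponding to an odds ratio of 1.59 per SD.

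In both, state that the calculation applies to the roughly 538 participants expected to have MCI (17% of 3165), and that the test is two-sided if that is what was used. The sponsor should confirm the choice against the original calculation, since the formula and sidedness are reconstructed here. The cost is one sentence in the protocol and wherever it is repeated, with no change to N. The first version lowers the stated detectable difference from 5 to 4.3 percentage points; the second raises the stated power.
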